**4.5. Data Collection:**

Feasibility outcomes will be collected and documented throughout the study by the research coordinator. The Lymfit server will store the Fitbit metrics, questionnaires responses will be collected at baseline, and at 12 weeks.

**4.5.1. Feasibility:**

This outcome will be assessed by 1) retention rate, 2) technical issues, and 3) safety (i.e., adverse events). In the bi-weekly meeting with the kinesiologist, participants will be instructed to report any adverse events during the intervention. Any technical and safety issues will be documented in a study log by the study coordinator and the kinesiologist.

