**4.0 Research Plan:**

**4.1. The Lymfit Intervention:** Both supervised training (*i.e.,* a coach) and activity trackers (*e.g.,* Fitbits) has great potentials improve adherence to exercise prescriptions (8,9). Each participant will be given a 12-week exercise program, which will be constructed based on the recommendations from the FITT guidelines for cancer survivors by a kinesiologist. The participants in the study will follow up with the kinesiologist every two weeks to discuss any necessary changes within the exercise prescription.

**4.2. Methodology:** This single arm proof-of-concept trial will be a phase one study of a larger randomized controlled trial (RCT). Ethics approval will be obtained from the Research Ethics Board (REB) at the Jewish General Hospital (JGH; Montreal, Quebec). Participants in the study will be prescribed a personalized exercise program for 12-weeks, and their physical activity will be monitored using a FitBit. We have recently developed “Lymfit”, a server that allows our team to retrieve and store data from Fitbit devices on a secure network at the JGH. Physical parameters including activity minutes, daily step counts, sleep time, sedentary minutes, will be collected from the participant’s Fitbit and are stored in the Lymfit server. To preserve patient confidentiality, we will de-identify patient data by assigning each patient’s Fitbit device with a name (*e.g.* Lymfit001) and an email (*e.g.* [contact]), such that Fitbit has no access to personal patient data other than the date of birth, height and weight. The participants will complete a set of study questionnaires at **baseline, and at 12-weeks** (post-intervention).

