We will ask patients to perform their baseline activity assessment during the first week with their Fitbit. After that first week, the kinesiologists will examine the baseline physical activity and sedentary behaviours of the patient and schedule an appointment with him/her using teleconferencing (e.g. zoom) due to the physical distancing measured imposed by the covid19 pandemic. The default intervention in the Fitbit tracker is to track and motivate participants to increase their activity each week until they reach the guidelines set for cancer patients (90 min/week). They will be given personalized instructions for exercise prescriptions based on their baseline fitness level and exercise history at baseline, and every two week-there-after (given by teleconferencing). For instance, for sedentary patients or symptomatic patients that lack any motivation to exercise, the initial goal would be to increase the step count and to decrease sitting time. The kinesiologist and patient can explore opportunities throughout the day to take a series of brief walks. As these small milestones are achieved, the goal would be to increase the duration of activity (more steps) and to increase the intensity of the activity (i.e. increase the heart rate to be considered “active” minutes by increasing the pace of walking or by walking up stairs). In more active patients, exercise will be tailored accordingly, and will not require that the patient engage in these activities at a gym, where exposure to potentially infectious contacts is increased. In motivated patients who have successfully achieved 90 min of MVPA/week, we will encourage them to gradually increase their activity to 50 min x 3 times/week to meet the Canadian general population guidelines (16). For the purpose of this study, Fitbit data will be collected from 0 to 12-weeks during the exercise intervention. Patients will be contacted by email if there is no activity detected from their Fitbit for over 12 hours and when the battery level is too low.

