**9.0. Compensation:**

# Participants will be provided with Fitbits pedometers, which they will keep even at the end of the project. This is to ensure that there is no infectious contamination between participants if these devices were to be re-used. Participants won’t be financially compensated for their time or transportation. All interventions will be done remotely (e.g., by zoom) to minimize social contact and risk of Covid transmission.

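### Adverse-event reporting is tied to the bi-weekly kinesiologist meeting, so no question is described for participants who stop attending, and safety may be under-recorded in them

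*Protocol*

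**What the plan says.** Protocol section 3.0 makes feasibility the primary objective and adds an aim of looking at safety problems with the remote programme. Section 4.5.1 defines feasibility by retention, technical issues and safety, the last meaning adverse events. On how events are raised it says: "In the bi-weekly meeting with the kinesiologist, participants will be instructed to report any adverse events during the intervention". On how they are recorded it says: "Any technical and safety issues will be documented in a study log by the study coordinator and the kinesiologist". Section 4.5 adds a general statement: "Feasibility outcomes will be collected and documented throughout the study by the research coordinator".

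The meeting named in 4.5.1 is also the point at which exercise is prescribed. Section 4.1 says: "The participants in the study will follow up with the kinesiologist every two weeks to discuss any necessary changes within the exercise prescription". Section 4.4 has the personalised instructions given at baseline and "every two week-there-after (given by teleconferencing"). Section 9.0 confirms that there is no in-person contact: "All interventions will be done remotely (e.g., by zoom) to minimize social contact and risk of Covid transmission".

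The other data contact is the questionnaires: "questionnaires responses will be collected at baseline, and at 12 weeks".

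**The concern.** Section 7.0 names fainting, dizziness, abnormal blood pressure and injury as possible harms. Any of these could lead a participant to stop exercising and to skip the next video call. The call is both where exercise is prescribed and where events are raised, so the act of stopping removes the participant from the described point of enquiry. Missing reports would then be linked to the events themselves, and the record would tend to look safer than the truth.

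Two parts of one outcome also become entangled: a drop-out counts against retention while its cause may never reach the safety log. Section 4.2 presents this study as the first phase of a larger randomised trial, so the record has a direct use. An event not asked about promptly may not be recoverable at analysis.

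**Working it through.** The protocol states no figure on this point, so there is nothing to reproduce. The check is whether any described contact puts an adverse-event question to a participant who has stopped attending.

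| Contact or route | Section | Reaches someone who stops attending? | Described as asking about adverse events? |
|---|---|---|---|
| Bi-weekly kinesiologist meeting | 4.1, 4.4, 4.5.1 | No | Yes |
| Coordinator's collection throughout the study | 4.5 | Possibly; no contact or trigger described | No |
| Study log | 4.5.1 | Does not apply; it records what is already known | No |
| Email after 12 hours without Fitbit activity, or on low battery | 4.4 | Yes if the device is off; not if it is worn without exercising | No |
| 12-week questionnaires (PROMIS-29, FCRI, FCV-19S) | 4.5, 4.5.3 | Possibly | No; pain interference and fatigue are covered, events are not |
| Relay of abnormal heart rate, or of extreme anxiety or depression, to the hematologist | 10.0 | Heart rate only if the device is worn | No |
| Lost-to-follow-up rule (more than four invalid weeks of 12) | 5.0 | It is a classification, not a contact | No; no enquiry into the reason is described |

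No row combines reaching the participant with asking the question.

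**Schedule.** Section 4.4 opens with a baseline week: "We will ask patients to perform their baseline activity assessment during the first week with their Fitbit". The protocol can be read in two ways.

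- Baseline is week 0 and the 12-week programme follows. Follow-up meetings fall at weeks 2, 4, 6, 8, 10 and 12, so 12 / 2 = 6 occasions. A full attender has 12 − 12 = 0 weeks uncovered.
- Baseline is week 1 of 12. Meetings fall after weeks 1, 3, 5, 7, 9 and 11, leaving 12 − 11 = 1 week uncovered, but only 12 − 1 = 11 prescribed weeks.

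The first reading fits better: section 4.1 promises a 12-week programme and section 5.0 counts from week 0 to week 12. On that reading, the stretch with no described question after a last attended meeting at week *k* is 12 − *k* weeks: 10 weeks for *k* = 2, 6 for *k* = 6, 2 for *k* = 10.

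**Illustration only.** Assume a true event proportion of 10% among the 20 planned participants, and let *d* be the assumed share of events that reach the log. The chance of logging at least one event is 1 − (1 − 0.10*d*)^20:

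- *d* = 1: 1 − 0.90^20 = 88%
- *d* = 0.75: 1 − 0.925^20 = 79%
- *d* = 0.50: 1 − 0.95^20 = 64%

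Both the 10% and the values of *d* are assumptions. The figures show sensitivity and do not estimate under-recording in this trial.

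**The case against.** The best reply is that section 4.5.1 does not confine reporting to meetings. It can be read as saying when participants are told to report, with the instruction then standing for the whole intervention. The coordinator, who is not described as prescribing exercise, collects feasibility outcomes throughout and shares the log, so capture is not left to the kinesiologist alone. The inactivity email already reaches some people who disengage, and abnormal heart rates go to the treating hematologist. Participants also stay in clinical care. The study is small and single-arm, uses gradual, tailored exercise after medical clearance, and sets no safety threshold.

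Much of this stands, and it narrows the point. What remains is that every alternative depends on a disengaged participant volunteering the event or on its surfacing incidentally. No route from the clinic to the study log is stated. An unseen SAP does not help, because whom to ask and when is data collection, which this protocol fixes itself.

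A reader might infer more than the text supports:

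- *That events outside meetings cannot be captured.* The routes above may capture some.
- *That the safety record is biased.* Under-recording is a risk with a plausible direction; nothing shows that it will occur.
- *That even full attenders have an unasked final week.* This needs the reading that fits the 12-week programme less well.

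**Conclusion.** The point holds in limited form. As written, section 4.5.1 ties adverse-event reporting to the contact that a participant loses on stopping the intervention, and no other described contact asks the question. Safety, a component of the primary feasibility outcome, may therefore be under-recorded in those who stop.

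The size cannot be derived: the protocol gives no expected attrition, event rate or share of events captured. What can be stated is that a participant last seen at week *k* has 12 − *k* weeks with no described question, while full attenders have none on the better-fitting reading.

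The conclusion rests on the visible protocol. The consent pages are not shown and could carry a reporting instruction, though such an instruction would still rely on the participant to come forward. The change is worth making before enrolment; the gap does not invalidate the design.

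**What to change.** In section 4.5.1, adopt one standard question for every enrolled participant: any adverse event since the last contact, and did it lead you to stop or cut back exercise?

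- The kinesiologist asks it at each bi-weekly meeting.
- The coordinator asks it by email after a missed meeting.
- The coordinator asks it at withdrawal.
- It is added as one item to the 12-week questionnaires for everyone who still agrees to contact, whether or not their Fitbit weeks are valid.

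For each event, note relatedness to exercise.

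The cost is about one email per missed meeting, one question at withdrawal and one questionnaire item, all with existing staff. The downside is that some chemotherapy symptoms will be picked up, because section 4.3 admits patients still on treatment; the relatedness note handles this.

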**4.5.2. Fitbit Metrics:**

Metrics, including light activity (minutes/day), MVPA (minutes/day), sedentary time (hours/day), total sleep time (hours/day), and steps taken (steps/day) will be captured via the Fitbit trackers and stored on the Lymfit server. Participants will be instructed to sync their Fitbit to the smartphone application daily to allow the captured data to be transferred to the Lymfit server.

**4.5.3. Self-Reported Health Outcomes:**

*Quality of Life:* QoL will be evaluated using the 29 items Patient-Reported Outcomes Measurement Information System® (PROMIS–29 Profile v2.1) obtained from the PROMIS Health Organization (<https://www.promishealth.org>) (10). The PROMIS measure perceived health status along seven domains, with items answered on five-point Likert scales. There are four items on each of the following domains: ability to participate in social roles/activities, anxiety/fear, depression/sadness, fatigue, pain interference, physical function, and sleep disturbance. PROMIS measures have been validated in >5000 people with lymphoma and other cancers, has robust psychometric properties and has been calibrated specifically in a large population-based cohort of people recently diagnosed with lymphoma and other cancers, and cancer patients beginning an exercise program (11,12).

*Fear of Cancer Recurrence (FCR):* The Fear of Cancer Recurrence Inventory (FCRI) was developed to assess the multidimensional aspects of FCR. The FCRI consists of seven subscales: triggers, severity, psychological distress, coping strategies, functioning impairments, insight, and reassurance. The 42 items are rated on a 5-point Likert scale ranging from 0 to 4. The FCRI is a reliable and valid self-report scale (13).

*Fear of Covid 19:* Fear related to the pandemic will be assessed using the Fear of COVID scale (FCV-19S) (14), a seven-item scale assessing the fear of COVID–19. The items are rated on a five-point Likert scale ranging from “1: strongly disagree” to “5: strongly agree” with total scores ranging from 7 to 35. Higher total scores represent higher levels of fear.

**5.0. Data Analysis:**

Descriptive statistics will be used to provide a summary of the basic demographic and physical characteristics of study participants. For the feasibility outcomes, the retention rate will be calculated as a percentage of the total number of those who are initially enrolled, and any technical and safety issues will be documented by the study coordinator. Physiologic metrics will be reported using descriptive statistics (i.e., frequency, percentage, mean, standard deviation). For all metrics captured by the Fitbit (i.e., light activity, MVPA, sedentary time, total sleep time, and steps taken), the daily averages will be computed from week 0 to week 12.

Missing data: Any day with a daily step count less than the pre-determined cut-off of 1000 steps/day will be excluded from the daily average over a week. A day will be included in the seven-day average only if the participant had more than 1000 steps in the day. A cut-off point for four out of seven days will also be required for that week to be considered a valid daily average. If there are less than four valid days of data for that particular week, that week of data for that participant will be omitted in the analysis. If a non-compliant participant had more than four invalid weeks out of the 12 weeks, they will be considered a lost to follow-up.

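### Section 5.0 judges whether a day is valid by its step count alone, so worn but inactive days are deleted along with unworn ones and a compliant, inactive wearer can be classed as lost to follow-up

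*Protocol*

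**What the plan says.** Section 5.0 sets three linked rules under Missing data.

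- **Day:** "Any day with a daily step count less than the pre-determined cut-off of 1000 steps/day will be excluded". It then restates this as "A day will be included in the seven-day average only if the participant had more than 1000 steps in the day". The two sentences disagree only for a day of exactly 1000 steps.
- **Week:** at least four of seven valid days are needed, and a week with fewer is dropped for that participant.
- **Participant:** "If a non-compliant participant had more than four invalid weeks out of the 12 weeks, they will be considered a lost to follow-up".

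No wear-time, heart-rate or other wear criterion appears in any of them.

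Section 4.5.2 lists steps among the five analysed metrics: "sedentary time (hours/day), total sleep time (hours/day), and steps taken (steps/day) will be captured via the Fitbit trackers", alongside light activity and MVPA. Section 4.3 admits patients who are on chemotherapy or have had it. Section 4.4 plans for inactive participants: "for sedentary patients or symptomatic patients that lack any motivation to exercise, the initial goal would be to increase the step count". It also provides for an email to the patient when there is "no activity detected from their Fitbit for over 12 hours", but section 5.0 makes no use of that prompt.

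Feasibility is the primary objective (section 3.0), and retention is the first feasibility outcome listed (section 4.5.1). Section 5.0 expresses retention as a percentage of those enrolled.

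**The concern.** A step cut-off is meant to screen out days when the tracker was not worn. Here it is the only criterion, and the screening variable is one of the outcomes. A worn day of 900 steps and a day with the device in a drawer are handled identically. Removing worn days from the bottom of the step distribution can only raise the average of the days that remain.

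The effect falls on the participants for whom section 4.4 sets more steps as the first goal. It is strongest where activity is lowest, so a real improvement from a sedentary start can be understated. Because the exclusion works on whole days, it also selects the days that enter the averages for light activity, MVPA, sedentary time and sleep.

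The rule also builds up over time: low-step days void weeks, and voided weeks turn a participant into a loss to follow-up. The word non-compliant in the participant rule gives no protection, since validity is judged by steps alone. The protocol does not spell out how this label enters the retention percentage. If it does, each participant misclassified among the 20 planned moves retention by 1/20 = 5 percentage points.

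**Working it through.** The protocol gives no step distribution and no computed figure on this point, so there is nothing to reproduce. The cut-off (1000), the week rule (4 of 7), the participant rule (more than 4 of 12) and N = 20 come from sections 5.0 and 4.3. Everything else below is an assumption.

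**1. One week, no distribution needed.** Take three worn days at 800 steps and four at 3000.
- All worn days: (3×800 + 4×3000)/7 = 14400/7 = 2057.
- Section 5.0 rule: 3000, since only the four high days remain.
- Overstatement: 3000/2057 − 1 = 46%.

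**2. A change can reverse sign.** Baseline week: three days at 900, four at 2000. Later week: three at 1100, four at 2000.
- True means: 10700/7 = 1529 and 11300/7 = 1614, a rise of 86.
- Section 5.0 rule: 2000 at baseline and 1614 later, an apparent fall of 386.

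**3. Size under an assumed distribution.** Daily steps X are gamma with mean m and coefficient of variation CV, so shape k = 1/CV² and scale m/k. Every day is fully worn. The share of days deleted is P(X < 1000). The mean of the retained days is m × P(Y > 1000)/P(X > 1000), where Y is gamma with shape k + 1 and the same scale. For m = 1500 and CV 0.5, k = 4 and scale = 375. This gives P(X < 1000) = 0.279 and a retained mean of 1500 × 0.868/0.721, about 1804, which is +20%.

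| True mean | Days deleted (CV 0.5 / 0.7) | Retained mean | Overstatement |
|---|---|---|---|
| 1500 | 28% / 38% | 1804 / 2062 | +20% / +37% |
| 2500 | 8% / 19% | 2650 / 2933 | +6% / +17% |
| 4000 | 2% / 9% | 4062 / 4321 | +2% / +8% |
| 7000 | 0.3% / 3.2% | 7018 / 7210 | +0.3% / +3.0% |

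A true rise from 1500 to 2500 (+1000) would be reported as 2650 − 1804, about +845 (CV 0.5), or 2933 − 2062 = +871 (CV 0.7).

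A lognormal model with assumed medians and CV 0.5 to 0.8 shows the same pattern: +13% to +25% at a median of 1500, +2% to +8% at 2500, at most +2.1% at 4000 and at most +0.3% at 7000.

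**4. Loss to follow-up for someone who always wears the device.** Let p be the share of days under 1000 steps, with days and weeks independent. P(valid week) = P(Bin(7, 1 − p) ≥ 4). P(lost) = P(Bin(12, 1 − P(valid week)) ≥ 5).

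| p | P(valid week) | P(lost) |
|---|---|---|
| 30% | 0.874 | 0.01 |
| 40% | 0.710 | 0.25 |
| 50% | 0.500 | 0.81 |

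Under the gamma model of step 3, P(lost) is 0.4% (CV 0.5) to 17% (CV 0.7) at a mean of 1500, and essentially zero at 2500 or more.

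**The case against.** A cut-off fixed in advance is a recognisable proxy for non-wear, and it does useful work. Unworn and partly worn days pull step averages down, and the rule removes some of them. The calculations above assume full wear and so count only one side. This stands: a reader might infer that the reported averages are known to be biased upward, but the documents support that only for the worn days that are deleted, not for the net effect in this cohort.

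The low-step scenarios may also be unusual. Participants were diagnosed at 18-39, are cleared for vigorous exercise, and may be past treatment, so it would be wrong to treat them all as a group on chemotherapy. At a mean of 7000 steps the effect is trivial. This also stands, although section 4.4 does expect some sedentary or symptomatic participants.

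The Fitbit metrics are descriptive, in a single-arm study of 20, with no stated decision resting on them. That limits the severity. It does not cover the retention route, which touches a feasibility outcome.

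Two further readings are tempting but not supported.

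- **The 12-hour prompt as a ready-made non-wear flag.** Section 4.4 describes an absence of activity, which a worn device on a resting patient might also produce.
- **Deterioration, and with it a safety signal, being concealed.** Adverse events are sought at the bi-weekly meetings (section 4.5.1), and abnormal heart rates and extreme anxiety or depression go to the hematologist (section 10.0). The section 5.0 rule governs the averages, not the monitoring.

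**Conclusion.** The point holds as a defect in a stated rule. Section 5.0 lets an outcome define its own missingness and cannot separate inactive days from unworn ones. For worn days the direction follows from the rule itself: average steps are overstated. The size depends on how active participants are. It is material at a true mean of about 1500 to 2500 steps per day, modest at 4000 and negligible at 7000, under gamma steps with CV 0.5 to 0.7 and full wear. The net effect in this cohort, after allowing for unworn days correctly removed, cannot be determined from the protocol.

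The retention consequence is confined to participants with a large share of low-step days. It becomes appreciable at around 40% of days and likely at 50%, if days are independent. It should be fixed, and it is not critical.

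**What to change.** Revise the Missing data paragraph of section 5.0.

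1. **If wear data can be retrieved:** define a valid day by evidence of wear that the device already records, such as a heart-rate or other recorded signal. Section 10.0 implies that heart rate is visible to the study, but section 4.5.2 does not list it among the stored metrics, so this needs confirming. Keep worn days whatever their step count, and report the 1000-step rule as a sensitivity analysis.
2. **If not:** keep the 1000-step rule and add a sensitivity summary that retains synced low-step days with non-zero recorded data.
3. **In either case:** do not count a participant as lost to follow-up for retention because of low-step days alone.
4. Do not use the 12-hour no-activity email as a non-wear flag by itself.
5. State which side of the cut-off a day of exactly 1000 steps falls on.

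The cost is one paragraph and some extra data processing. The drawback is that some partly worn days may enter and pull the averages down, which is why both summaries should be shown.

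### One step-count test decides which days are valid for all five Fitbit metrics, but it cannot detect unworn nights or part-day removal, which matter for sleep and sedentary time

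*Protocol*

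**What the plan says.** Section 4.5.2 defines the metrics. Two of them are totals in hours: "sedentary time (hours/day), total sleep time (hours/day), and steps taken (steps/day) will be captured via the Fitbit trackers". Section 5.0 then handles all five together: "For all metrics captured by the Fitbit (i.e., light activity, MVPA, sedentary time, total sleep time, and steps taken), the daily averages will be computed".

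The missing-data paragraph of section 5.0 sets three rules, each built on the one before:

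- Day: "Any day with a daily step count less than the pre-determined cut-off of 1000 steps/day will be excluded from the daily average over a week", restated as "A day will be included in the seven-day average only if the participant had more than 1000 steps in the day".
- Week: "A cut-off point for four out of seven days will also be required for that week to be considered a valid daily average".
- Participant: "If a non-compliant participant had more than four invalid weeks out of the 12 weeks, they will be considered a lost to follow-up".

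None of these is limited to steps or activity. The protocol gives no minimum wear time, no night-wear condition and no rule for a day without a sleep record. The only other provision on non-wear is in section 4.4: an email to the participant after more than 12 hours without detected activity, or when the battery is low. That prompt excludes no data.

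**The concern.** A step count is reasonable evidence that the tracker was worn for part of the day. It is no evidence that it was worn at night, or for the remaining waking hours. Total sleep and total sedentary time both depend on those hours. A participant who passes the step threshold and then removes or charges the tracker overnight has a valid day for sleep with no sleep observed.

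The stakes are in interpretation. Reducing sitting time is an early goal for sedentary patients in section 4.4, so sedentary hours are likely to be read as a response to the programme. The study has a single arm of 20 participants. If wear drifts over the 12 weeks, no control group can separate that drift from a change in behaviour. Night wear is also useful feasibility information for the larger trial, and these rules would not show it.

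**Working it through.** The protocol gives no figure to reproduce here. The arithmetic below shows what the stated rule allows. Every input not taken from the protocol is marked as an assumption.

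**1. Wear needed to pass the day test.** Threshold from section 5.0: more than 1000 steps. Assumed cadence: 60 to 120 steps/min.

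- Minutes = 1001 / cadence: 1001/120 = 8.3 min; 1001/60 = 16.7 min.
- Share of 24 h: 8.3/1440 = 0.6%; 16.7/1440 = 1.2%.

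A day with the tracker off nearly all day or all night can therefore pass. This shows what is possible, not how often it happens.

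**2. Sleep.** Let S be true sleep per night (assumed 7.0 h, range 6 to 8 h), n the step-valid days in the week (4 to 7, section 5.0) and k the unworn nights among them.

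- Unworn nights scored zero: mean = S × (n − k)/n.
- Unworn nights blank: mean = S, assuming worn and unworn nights have the same sleep on average, but it rests on n − k nights.

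| n | k | Mean if zero (S = 7.0 h) | Change | Loss for S = 6 to 8 h | Mean if blank | Nights behind it |
|---|---|---|---|---|---|---|
| 7 | 1 | 6.0 h | -14% | 0.86 to 1.14 h | 7.0 h | 6 |
| 7 | 2 | 5.0 h | -29% | 1.71 to 2.29 h | 7.0 h | 5 |
| 7 | 3 | 4.0 h | -43% | 2.57 to 3.43 h | 7.0 h | 4 |
| 4 | 1 | 5.25 h | -25% | 1.5 to 2.0 h | 7.0 h | 3 |
| 4 | 3 | 1.75 h | -75% | 4.5 to 6.0 h | 7.0 h | 1 |

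With zero coding the mean is biased downwards. With blank coding it is not, but the last two rows show a week passing the four-day rule on three recorded nights or one. The four-of-seven safeguard counts step-days, so it does not protect the sleep average under either coding.

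**3. Sedentary time.** Let h be the waking hours unworn on a valid day (assumed 8) and f the share of them that was really non-sedentary (assumed 20% to 40%).

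- Non-wear counted as sedentary: overcount = h × f = 8 × 0.2 to 8 × 0.4 = 1.6 to 3.2 h that day.
- Non-wear not counted: undercount = h × (1 − f) = 8 × 0.8 to 8 × 0.6 = 6.4 to 4.8 h that day.

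The sign depends on coding, which the protocol does not state.

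**4. The email prompt.** It needs more than 12 hours without activity. A night off of ordinary length, or a shorter daytime gap, would not trigger it.

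**The case against.** The strongest reply has four parts.

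- **The day rule is a necessary condition.** It says a day counts only if steps exceed 1000, so a statistical analysis plan could add a wear or sleep-record condition. This is fair as logic. However, the protocol fixes the step count as its one stated test, applies it to all five metrics and builds the week and participant rules on it. Followed as written, it accepts sleep and sedentary days that it cannot screen.
- **The large bias is conditional.** A reader might infer that mean sleep will be about 29% too low. The documents do not support that: the figure needs unworn nights to be scored zero, and nothing says they are. With blanks there is no such bias.
- **There is some protection.** A reader might also infer that sleep and sedentary time have no validity rule at all. That goes too far. The step test removes days with little or no wear for every metric, and the emails and daily syncing should reduce long gaps. The gap concerns night and part-day non-wear.
- **The consequence is limited.** The primary objective is feasibility, judged on retention, technical issues and safety. The Fitbit metrics are descriptive, with no test or threshold attached to sleep or sedentary time. This stands and limits the weight of the point.

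It would also be wrong to assume that a waking-wear minimum can simply be applied to data in hand. Section 4.2 lists activity minutes, steps, sleep time and sedentary minutes, but not wear time. Section 10.0 implies that heart rate is seen, without saying that minute-level data are stored.

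**Conclusion.** The point holds: one step-based test is used for two metrics it cannot adequately validate. What follows from the text alone is that a week can be valid for sleep with fewer than four recorded nights, and that sedentary hours shift with unworn time. The size depends on coding that the protocol leaves unstated. For 7.0 h of true sleep and 2 of 7 nights unworn, the range runs from no bias (blank nights) to 5.0 h, or -29% (zero nights). How often such nights occur is unknown.

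The primary outcomes are affected only indirectly: the lost-to-follow-up rule is also judged on steps, so poor night wear does not register as non-compliance. The rule should be changed because the sleep part is cheap to correct, but it does not threaten the study's main conclusion.

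**What to change.** Amend the missing-data paragraph of section 5.0 as follows.

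1. **Sleep.** Average only nights with a recorded sleep period. Treat a night without one as missing, never as zero. Require at least four such nights for a valid sleep week.
2. **Sedentary time.** State how unworn time enters sedentary minutes. Where the retrieved data allow wear time to be derived, apply a waking-wear minimum set in advance, or report sedentary time as a share of worn waking time. Where they do not, report sedentary time with that limitation stated.
3. **Reporting.** Give the number of valid nights and valid days by week beside these metrics, so that drift in wear can be seen.

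This point asks for no change to the step test for step counts.

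The cost is a few lines of text and the loss of some nights or days. The sleep rule uses the sleep value already collected. The sedentary rule may need data that the protocol does not list as retrieved, which is why it has a fallback.
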